#### Secondary outcome measures

The secondary outcome measures are as follows:
Related indicators of immunosuppression include interleukin (IL)-6, IL-10, C-reactive protein (CRP), postoperative infectious complications (pneumonia, incision infection, and indwelling catheter infection), ICU stay time, and mortality. The examination methods and time points are as follows:
IL-6 and IL-10: Plasma levels of IL-6 and IL-10 will be determined using the ELISA (enzyme-linked immunosorbent assay) with high sensitivity kits (ABCAM, Shanghai, China) one day before surgery and on Days 1, 3, and 5 after surgery.CRP: CRP expression level in blood samples, determined with automatic biochemical analyzer (Beckman Coulter, Atlanta, GA, USA), one day before surgery and on Days 1, 3, and 5 after surgery.Postoperative infectious complications:
Pneumonia: Pneumonia was defined according to the Centers of Disease Control and Prevention (CDC) guidelines [58]. Postoperative healthcare-associated pneumonia will be assessed throughout by radiograph suspicious for pneumonia, clinical signs and symptoms suspicious for pneumonia and positive culture from bronchoalveolar lavage, a positive blood culture not related to another infection, or a positive sputum culture.Postoperative infection other than pneumonia: observe the incidence of incision infection and indwelling catheter infection after the surgery (fever, bacterial culture).We will record postoperative infectious complications according to the patient’s medical history, imaging examination, clinical signs, and sputum culture within 30 days after the operation.ICU stay time: We will record the length of ICU stay after surgery (days [*d*], mean ± standard deviation [SD]).Mortality: We will record a 30-day mortality rate after surgery.The indicators of related mechanisms studied include high mobility group box 1 proteins (HMGB1), regulatory T cells (Treg), and CD4^+^ T cells. The examination methods and time points are as follows:
HMGB1: HMGB1expression level in blood samples, ELISA kit (ABCAM, Shanghai, China) one day before surgery, and on Days 1, 3, and 5 after surgeryTreg: Percentage of CD4^+^/CD25^+^ T cells in CD4^+^ T cells, flow cytometry (Becton-Dickinson, Franklin Lakes, NJ, USA), one day before surgery and on Days 1, 3, and 5 after surgeryCD4+ T cells: CD4+ T cell number/ml blood, flow cytometry (Becton-Dickinson), one day before surgery and on Days 1, 3, and 5 after surgery.

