### Statistical analysis

All statistical analyses of the data will be performed using SPSS program V.21.0 (SPSS Inc., Chicago, IL, USA). A *P* value < 0.05 will be considered statistically significant. The intention-to-treat (ITT) approach will be used. Measured data will be expressed as mean ± SD (^−^*x*± *s*) if it obeys a normal distribution or an approximate normal distribution. The median (interquartile range [IQR]) will be used if the data do not obey the normal distribution and count data will be expressed in terms of the number of cases.

To analyze the primary outcome, the expression of mHLA-DR (the percentage of HLA-DR+/CD14+ cells in all CD14+ cells) will be calculated by repeated measures analysis of variance (ANOVA), and the comparisons between the two groups will be made using the Student’s *t* test. For the secondary outcomes, we will use chi-square tests for categorical data and repeated measures ANOVA or the Wilcoxon rank sum test for continuous data, according to whether the data are normally distributed. The variance analysis will be performed for the difference between the two groups and within a group. A stratified analysis will be performed to control the confounding factor if necessary. Data analysis will be conducted by statisticians who are independent of the research team.

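### A normality check on the trial data selects the test for continuous secondary outcomes; for the repeated markers its two branches answer different questions, and for ICU stay the ANOVA branch cannot be run

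*Protocol article*

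**What the plan says.** The protocol article, under Statistical analysis, assigns continuous secondary outcomes to "repeated measures ANOVA or the Wilcoxon rank sum test for continuous data, according to whether the data are normally distributed". For description, the same section gives mean ± SD for normal or approximately normal data; the median (IQR) "will be used if the data do not obey the normal distribution".

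The Secondary outcome measures section describes two kinds of continuous outcome:

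- **Repeated markers.** IL-6, IL-10 and CRP are sampled "one day before surgery and on Days 1, 3, and 5 after surgery". HMGB1, Treg and CD4+ T cells follow the same four-point schedule.
- **ICU stay.** "We will record the length of ICU stay after surgery", in days, with the summary fixed without condition as "mean ± standard deviation [SD".

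Death is a separate outcome: "Mortality: We will record a 30-day mortality rate after surgery". The analysis principle is stated as "The intention-to-treat (ITT) approach will be used". The article does not say how a death in the ICU enters the ICU-stay comparison.

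**The concern.** One sentence covers outcomes of different structure and lets the observed distribution decide what is tested. For a four-time-point marker, repeated measures ANOVA asks whether the arms follow different courses over baseline and Days 1, 3 and 5. A rank sum test asks whether one arm tends to have higher values on a single quantity, and the rule does not name that quantity (a day, a change from baseline or a summary). Two markers, or two time points of one marker, could therefore be analysed for different quantities only because one looked more skewed. If the unnamed day becomes every postoperative day, each marker brings three tests at 0.05.

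For ICU stay, the rule names a test that needs repeated values, and two sections prescribe different summaries. These are secondary outcomes, so the primary conclusion is not at risk. At stake are the interpretability of the marker results and some efficiency, since a pre-surgery value is collected and the Wilcoxon branch need not use it.

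**Working it through.** The article gives no figure for these outcomes to reproduce, and no distribution for any marker or for ICU stay. The first step is a comparison of sections; the others are illustrations on stated assumptions.

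**1. Rule against outcomes.**

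| Outcome | Values per patient | Branch if normal | Branch if not normal |
|---|---|---|---|
| IL-6, IL-10, CRP, HMGB1 | 4 | Repeated measures ANOVA: runs, tests a profile | Wilcoxon: time point or contrast not named |
| ICU stay | 1 | Repeated measures ANOVA: no repeated factor, cannot be run | Wilcoxon: runs, valid two-sample test |

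ICU stay has mean ± SD fixed in its definition, while the general rule gives median (IQR) for non-normal data. The two agree only if stay is close to normal.

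**2. Power on one postoperative day.** Assumptions: log-normal marker; 40 per arm (44 × 0.9 = 39.6, from the stated 10% dropout); two-sided 0.05; standardised log-scale effect d = 0.634, chosen because it gives 80% power unadjusted.

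- Unadjusted t test on the log scale: noncentrality d√(n/2) = 0.634 × √20 = 2.835, power 80%.
- Wilcoxon: relative efficiency 3/π = 0.955, noncentrality 2.835 × √0.955 = 2.771, power about 78%. Simulating the switch itself (Shapiro-Wilk in each arm, then a t test or Wilcoxon) also gives about 78%.
- Log scale adjusted for the pre-surgery value with correlation ρ: the effect becomes d/√(1 − ρ²).
  - ρ = 0.3: 0.634/0.954 = 0.665, noncentrality 2.972, power about 83% (the formula gives 83.5%, ignoring the small cost of estimating the slope).
  - ρ = 0.5: 0.634/0.866 = 0.732, noncentrality 3.274, power 89-90%.

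The gain over the switched test is about 5 points at ρ = 0.3 and 11-12 points at ρ = 0.5. It comes from using baseline. The log scale alone adds only about 2 points (80% against 78%).

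**3. False positives if the unnamed day becomes all three.** For independent days, 1 − 0.95³ = 14.3%. Simulated with 44 per arm, log-normal markers, within-patient correlation 0.5 and no effect:

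- Wilcoxon at 0.05 on Days 1, 3 and 5: at least one false positive in 12-13% of trials.
- The two-stage rule (Shapiro-Wilk at each time point, then ANOVA or three Wilcoxon tests): 9-13%.
- The group-by-time ANOVA test alone: about 4-5%.

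**4. Size of the ICU-death query.** Assumptions: log-normal stay, median 3 days, log-scale SD 0.6, 44 per arm, equal stay in survivors, deaths entered as 0.2 to 1 day and all in the control arm.

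| Control deaths | Control arm looks shorter by (days, mean) | Wilcoxon rejection |
|---|---|---|
| 1 | 0.06 | 4.7% |
| 2 | 0.14 | 5.5% |
| 4 | 0.27 | 9.0% |

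**The case against.** The strongest reply is that the sentence is a condensed menu and does not claim that each test fits each outcome. A skewed ICU stay would go to the Wilcoxon test with median (IQR), which is what this point asks for. If stay were judged normal, the section's general remark about variance analysis between the groups could be read as a one-way ANOVA. The day or contrast for Wilcoxon could be set in an analysis plan that is not shown, and change from baseline is compatible with the text. The trial is described as preliminary and the outcomes are secondary.

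Much of this stands. It would be wrong to infer that the rule cannot handle ICU stay at all: only its ANOVA branch fails. Visit-by-visit Wilcoxon testing is one plausible reading, not a stated plan, so the 13% is conditional on it. What does not fall away is the switch itself. An analysis plan could name the day, but it could stop the data choosing between two different questions only by replacing the published rule.

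Two further inferences are tempting and unsupported:

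- **That the plan counts an early ICU death as a short stay.** The article is silent. Raw length of stay under intention to treat would have that effect by default, but the handling of deaths may be left to the analysis plan, and mortality is reported separately.
- **That skewed markers would lose much power through raw-scale ANOVA.** Under the rule, clearly skewed markers would usually move to Wilcoxon, so the loss against an unadjusted log-scale test is only about 1-3 points. How often the switch occurs cannot be fixed either: no normality test is named, and the article gives no marker distributions.

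**Conclusion.** The point holds as a poorly fixed rule for secondary outcomes. The choice between repeated measures ANOVA and Wilcoxon depends on the trial data. For the repeated markers the branches estimate different things, and the Wilcoxon branch leaves its time point or contrast open. For ICU stay the ANOVA branch is not runnable, and the fixed mean ± SD must be reconciled with the median (IQR) rule.

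The size is moderate and rests on assumptions that the article can neither confirm nor refute: log-normal markers, baseline correlations of 0.3 to 0.5, and an effect set to give 80% power unadjusted. On these, one baseline-adjusted log-scale analysis has about 83% to 90% power against about 78%. It also avoids a chance of about 13% of at least one false positive per marker if all three postoperative days are tested by Wilcoxon at 0.05.

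ICU death remains a query, not an error. The illustrated bias is small unless several deaths fall in one arm.

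**What to change.** In the Statistical analysis section:

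1. Delete the normality-dependent choice of test.
2. Analyse IL-6, IL-10, CRP and HMGB1 on the log scale with one prespecified longitudinal model that includes group, time and their interaction and adjusts for the pre-surgery value. Name the contrast to be reported and give geometric mean ratios with confidence intervals. Treg and CD4+ T cells come under the same rule and also need one prespecified analysis.
3. Analyse ICU stay by the Wilcoxon rank sum test with median (IQR), and amend the mean ± SD in its outcome definition to match.
4. As a query, state how deaths in the ICU enter the stay analysis. A sensitivity analysis giving those patients the worst rank would suffice.

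The cost is wording only. No sampling, visit or sample size changes. The one small downside is that marker effects are reported as ratios and not as differences in the original units.

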### Data collection and management

The data will be collected as primary and secondary outcome measures, with the above-described method. All data will be saved safely on an internal server of Shuguang Hospital, with complete confidentiality. The participants of this study will be cited with a code different from their real names. The data management program will be approved by the trial manager and other clinicians before the registration of the first participant.

### Adverse events

The status related to adverse events is acquired according to the self-report of the patient or direct observation of clinicians or by non-induced query of the patient, and his/her clinical safety will be evaluated (see Table 1).

**Table 1 Tab1:** Clinical safety evaluation in perioperative period: any of the listed conditions is considered a *complication of the perioperative period*

1	Postoperative arrhythmia	Postoperative atrial fibrillation, atrial flutter, supraventricular tachycardia, ventricular tachycardia, ventricular fibrillation, ventricular flutter, cardiac arrest, atrioventricular block of 2^nd^ degree or above, frequent atrial premature beat and ventricular premature beat significantly affecting the stability of hemodynamics (indicated in electrocardiogram [ECG])		
2	Pneumonia	Body temperature above 38.5 °C (indicated in chest film)		
3	Acute lung injury	(1) Acute onset, with pathogenic factors		
		(2) Oxygenation index (arterial partial pressure of oxygen/fraction of inspired oxygen, PaO_2_/Fi0_2_) < 300 mmHg (1 mmHg = 0.133 kPa) not referring to positive end-expiratory pressure (PEEP) level		
		(3) Frontal X-ray chest film revealed patchy shadows in both lungs		
		(4) Pulmonary artery incarceration pressure < 18 mmHg or no clinical evidence of increased pressure in left atrium		
		(5) Acute paroxysmal respiratory failure		
4	Pulmonary atelectasis	Indicated in chest film		
5	Intraoperative and postoperative myocardial infarction	Manifestation of myocardial infarction symptoms or change of ECG ST segment, continuous increase of myocardial enzyme, especially cardiac troponin I (cTnI), accompanied with dynamic change of ST segment		
6	Postoperative cardiac insufficiency	The postoperative cardiac output (CO) is lower than lower limit of normal value or there are symptoms and vital signs of heart failure	(1) Left cardiac insufficiency	*Symptoms*: dyspnea; coughing, expectoration, and hemoptysis; cyanosis, fatigue, and weakness
				*Vital signs*: expansion of border of cardiac dullness, left lower shifting of cardiac impulse with elevating sensation. Accelerated heart rate, diastolic gallop heard in apex, alternative pulse in severe case. Moist and dry rales are heard in the bottom of both lungs. Wheezing rale and dry rales may be accompanied with secondary bronchial spasm
			(2) Right cardiac insufficiency	*Symptoms*: reduced urine volume, increased nocturnal enuresis, swelling pain in liver region or even occurrence of jaundice; inappetence, dyspepsia, nausea, vomiting and diarrhea
				*Vital signs*: expansion of border of cardiac dullness, apex beating showing elevating sensation, diffuse beating range, accelerated heart rate
				Distention of jugular vein, liver swelling with tenderness, hepatojugular reflux sign positive; pitting edema, right heart failure
				Typical vital signs of failure, mostly in the body drooping part
			(3) Whole cardiac insufficiency	Coexistence of clinical manifestations of left and right cardiac insufficiency, but principally one of them
7	Postoperative respiratory insufficiency	Patients showing intracardiac anatomical shunt and cardiac volume decrease when they breath in indoor air at static conditions will be excluded; arterial partial pressure of oxygen (PaO_2_) is lower than 8 kPa (60 mmHg) or accompanied with partial pressure of carbon dioxide (PaCO_2_) higher than 6.65 kPa (50 mmHg)		
8	Postoperative hemorrhage of digestive tract	Ulcer bleeding or bloody gastric content caused by mucosal ischemia of gastrointestinal tract, hematemesis, tarry stool or hemafecia		
9	Postoperative hepatic insufficiency	Severe hepatocellular damage, causing significant metabolism, secretion, synthesis, biotransformation, and immune function disorder, clinical syndrome of edema in the organism, jaundice, hemorrhage, infection, renal function disorder, and hepatic encephalopathy, etc.		
	Postoperative renal insufficiency	Rapid decrease of renal excretory function in short term, and daily mean increase of serum creatinine ≥ 44.2 μmol/L and exacerbation of existing renal insufficiency		
10	Postoperative infection other than lung infection	Including hematogenous infection, infections of digestive tract, urinary system, wound, skin, and indwelling catheter		
11	Postoperative cerebral ischemia and hypoxic disease	Including cerebral infarction, cerebral thrombosis, cerebral hemorrhage, transient cerebral ischemic attack, and diffuse cerebral ischemia and hypoxic disease		
12	Prolongation of postoperative hospital stay	Postoperative hospital stay exceeds 14 days		
13	Acute kidney injury	(1) Increase of plasma creatinine within 48 h ≥ 0.3 mg/dL (≥ 26.5 μmol/L)		
		(2) Plasma creatinine within 7 days ≥1.5 times the basic value		
		(3) Urine volume within 6 h lower than 0.5 ml/kg/h		
14	Death in perioperative period: definition	(1) Death within 30 days after surgery		
		(2) Death in hospital stay after surgery		
		(3) Death caused by surgical reasons after discharge		

### Quality control

The chief surgeon of the thoracic surgery department, the anesthetist to implement anesthetic management, the nurse of the anesthesiology department to carry out TEAS (having received specialized acupuncture training) as well as blood sampling personnel of clinical lab and data recording personnel are fixed to avoid bias from human operations. Specialized acupuncture training mainly includes selection of acupoints and the TEAS operation standard and procedure (see Table 2).

**Table 2 Tab2:** TEAS operation standard and procedure

1	Determination of position	The patient takes a supine position
2	Inspection of equipment	Confirm normal operation of electric acupuncture apparatus
3	Area and acupoint locating	The Zusanli acupoint and Shenshu acupoint are determined by feeling and pressing the point for acupuncture
4	Local skin preparation	Prepare the skin at the acupuncture point, disinfect from the center with 75% ethanol cotton ball in circle to wipe off the sebum
5	Selection of surface electrodes	Select surface electrodes specially used for TEAS
6	Acupoint patching	Attach the electrode slices specially used for TEAS on the acupoints, press to confirm they are securely attached
7	Connection of electrode slices to equipment	Connect Zusanli acupoint and Shenshu acupoint on one side to 2 electrodes of the same wire, and those of the other side to another 2 electrodes of the same wire; both wires are connected to the same electric acupuncture apparatus
8	Acupoint electric stimulation	Confirm the electric acupuncture apparatus is in power-up state, turn on the electric acupuncture apparatus, select corresponding parameters, and initiate TEAS therapy according to the patient’s tolerance to electric stimulation
9	Maintenance treatment	Maintain electric stimulation for 30 min, instruct the patient to protect the surgery area in acupuncture pin setting process, and closely examine the patient for adverse reactions of fainting, vomiting, and pain during acupuncture treatment; provide symptomatic treatment if needed
10	End of treatment	Turn off the electric acupuncture apparatus, remove the electrode slices, and clear away connection wires. Check redness and swelling or other injury on the skin where electrode slice was attached, and provide symptomatic treatment if these symptoms occur

## Discussion

Patients undergoing CABG with CPB are more prone to have immunosuppression, which may lead to postoperative infectious complications and a prolonged ICU stay, and even mortality. Previous studies have proved that acupuncture was able to improve patients’ immune function. TEAS has a similar efficacy as electroacupuncture, but it is easier to operate, non-invasive, and easy to accept by patients. The current study aims to evaluate potential TEAS-induced reversal of decreased mHLA-DR (a standardized “global” biomarker of immunosuppression) and explore the possible underlying mechanism related to TEAS.

Although the immediate clinical impact of this study is limited, its results will inform further research. Following demonstration of possible immunological efficiency, biomarker-guided immunological interventions of TEAS for immunosuppression should be performed in populations with sufficiently large sample size using relevant patient-centered clinical outcomes (e.g., mortality or infectious complications). Only in this way can we finally determine the clinical value of TEAS for counterbalancing CABG-associated immunosuppression and promote its application.

## Trial status

This is the third protocol version, updated on October 31, 2019. The recruitment began on December 1, 2017 and should be completed by December 31, 2019. At the time of manuscript submission, the study was in recruitment phase.

## Data Availability

The final trial dataset will only be accessible to the study investigators.

## Abbreviations

BMI: Body mass index
CABG: Coronary artery bypass grafting
CD4^+^ T cell: CD4 positive thymocyte cell
CPB: Cardiopulmonary bypass
CRP: C-reactive protein
FiO_2_: Fraction of inspired oxygen
GA: General anesthesia
HMGB1: High mobility group box 1 protein
IL-6: Interleukin 6
ITT: Intention-to-treat
mHLA-DR: Monocytic human leukocyte antigen DR
PCO_2_: Partial pressure of carbon dioxide
PO_2_: Oxygen partial pressure
RR: Respiratory rate
TEAS: Transcutaneous electrical acupoint stimulation
Treg: Regulatory T cell
VT: Tidal volume
